# Multi-modal integrated intervention combining exercise, anti-inflammatory, and dietary advice (MMIEAD) for adults with kidney cachexia: protocol for a mixed-methods feasibility cluster randomised controlled trial and process evaluation

**DOI:** 10.1186/s40814-026-01784-z

**Published:** 2026-02-19

**Keywords:** Cachexia, Multimodal interventions, Haemodialysis, Muscle wasting

## Abstract

**Background:**

Kidney cachexia is a debilitating and under-recognised complication of advanced chronic kidney disease (CKD), characterised by unintentional weight loss, muscle wasting, inflammation, and reduced functional capacity. Its profound impact on morbidity, quality of life, and healthcare utilisation underscores the need for targeted, implementable interventions. The multicomponent implementation strategy for a multi-modal, integrated, exercise, anti-inflammatory, and dietary advice (MMIEAD) intervention seeks to address this gap. Guided by the practical, robust implementation, and sustainability model (PRISM), which incorporates reach, effectiveness, adoption, implementation, and maintenance (RE-AIM) outcomes, this study aims to ensure strong intervention–context alignment to support future scalability.

**Methods:**

The MMIEAD model will be evaluated by determining patient eligibility and recruitment rates, identifying intervention retention and adherence, assessing key statistical and methodological considerations to inform optimal study design and data collection burden, conducting a qualitative process evaluation to examine intervention acceptability and practicality, and determining the feasibility of undertaking a definitive economic evaluation.

**Design:**

This mixed-methods study consists of three phases. Phase 1 will deliver and evaluate a 12-week multimodal intervention using a feasibility cluster randomised controlled trial (cRCT) design. Phase 2 will undertake a qualitative process evaluation with healthcare practitioners (HCPs) and patients. Phase 3 will assess the feasibility of conducting a full economic evaluation.

**Participants:**

Patients will be eligible if they have haemodialysis-dependent CKD stage 5 for more than 3 months, have experienced unintentional weight loss of at least 5% in the previous 12 months, or have a body mass index <20 kg/m^2^, and are aged over 18 years. HCPs will be eligible if they are members of the multidisciplinary healthcare team for more than 3 months and have had exposure to the study.

**Setting and randomisation:**

The study will be conducted across four outpatient haemodialysis units in the UK. Two sites have been randomly allocated to the intervention group and two to the control group.

**Sample:**

For phases 1 and 3, a total of 40 patient participants will be recruited (10 per intervention site and 10 per control site). For phase 2, qualitative data will be collected through interviews with approximately 15 patients and interviews or focus groups with 15 HCPs across all sites. Recruitment commenced on 08.09.25 following ethical approval (REC reference: 25/NI/0069).

**Discussion:**

Using multi-method analyses informed by PRISM/RE-AIM dimensions, we will generate evidence on the feasibility, acceptability, and contextual fit of the MMIEAD intervention to prepare for a definitive UK-wide multi-site cRCT.

**Trial registration:**

Trial registration number NCT07107087 (30 July 2025). https://clinicaltrials.gov/study/NCT07107087

**Supplementary Information:**

The online version contains supplementary material available at 10.1186/s40814-026-01784-z.

## Background

Pathological loss of muscle mass, or kidney cachexia, is a major contributor to morbidity, mortality (20% 1-year mortality rate), increased healthcare costs, and reduced quality of life [1]. Unimodal therapy has limited success in cachectic patient populations, given its multifactorial pathogenesis [2]. This has been recognised in chronic conditions such as cancer which have progressed to the development of clinical guidelines for cancer cachexia multi-modal interventions [3]. Patients with or at risk of cachexia must be supported to maintain body weight, improve strength, enhance the capacity for independent functioning, reduce frailty, stabilise abnormal biochemistry, and prolong survival [4]. Therefore, as systematic reviews and meta-analyses suggest the incorporation of a multi-component intervention, it is essential to address the complex pathophysiology of cachexia [5, 6]. However, currently no such licensed treatment or standard of care for cachexia in kidney failure exists. This is the first study to explore the potential use of a multi-modal, integrated, exercise, anti-inflammatory, and dietary advice (MMIEAD) intervention for kidney cachexia through a feasibility cluster randomised controlled trial (cRCT).

Brownson and colleagues [7] identify three types of evidence in implementation science: type one evidence on aetiology and burden; type two evidence on intervention effectiveness; and type three evidence on dissemination and implementation within context. Progression to a feasibility trial for kidney cachexia reflects more than a decade of evidence generation across all three domains. For type one evidence, our longitudinal pilot study [8] using a generic definition of cachexia in haemodialysis patients reported a 16% prevalence in a UK cohort, confirming kidney cachexia as a severe yet under-recognised condition. Complementary qualitative work including an international mixed-methods study exploring renal HCPs’ perceptions [9] and an interpretive phenomenological study involving patients and carers [10] further demonstrates the substantial burden of cachexia and the need for tailored interventions. Type two evidence has been informed by four reviews of multimodal cachexia interventions [11] which underpin the selection, duration, and structure of MMIEAD. Consistent with scientific consensus, multimodal approaches integrating exercise, nutritional support, and anti-inflammatory strategies are considered the most effective means of treating severe wasting [12]. Evidence suggests that these components act synergistically to improve nutritional and physical status, thereby enhancing quality of life [13]. Given that nutritional interventions alone do not improve longevity [14], active treatment must also target muscle loss [15] and the inflammatory pathways that drive cachexia [16]. Combining pharmacological and non-pharmacological components enables these multifactorial mechanisms to be addressed concurrently [17]. For type three evidence, we employed a theory of change (ToC) framework to strengthen intervention design and clarify the causal pathways underpinning implementation feasibility [18–20]. This work was guided by frameworks such as the Medical Research Council’s guidance on developing and evaluating complex interventions [21], the TIDieR checklist [22], and the SPIRIT 2025 guidelines [23]. Reporting the ToC in advance has enhanced understanding of both contextual influences and the intervention’s active elements [24]. Aligned with updated MRC guidance [25], the intervention theory was developed collaboratively with diverse stakeholders, including patient and public involvement and engagement (PPIE) representatives [20]. The resulting ToC map [20] outlines how core components and mechanisms interact with contextual factors and how these may influence implementation success.

To ensure optimum intervention-context alignment, we have interwoven the Practical, Robust Implementation, and Sustainability Model (PRISM) [26] which incorporates reach, effectiveness, adoption, implementation, and maintenance (RE-AIM) [27] outcomes into our trial design. Considering implementation science emphasises alignment of interventions to local contexts with an equity focus, this underscored a need to understand local contextual domains [28]. PRISM’s context-oriented approach has helped us to prepare accordingly for the intervention, for example, taking into consideration the attributes of those delivering and receiving the intervention and the infrastructure supporting the intervention [26]. We have actively demonstrated an ongoing and iterative engagement process with PPIE representatives through co-design and ongoing involvement in MMIEAD [26]. PPIE representatives’ priorities, needs, and values have been and continue to be deemed equally important alongside organisational perspectives, resources, and infrastructure because these factors impact an intervention’s uptake, equitable implementation, and impact [28]. Our approach has combined both a comprehensive approach that includes clinical, academic, and experiential expertise, as illustrated by our international expert reference group consisting of practicing nephrologists, physiologists, dieticians, clinical research nurses, PPIE representatives, and academics. The core aspects of RE-AIM which we have considered in this feasibility trial include the intervention’s reach, effectiveness, adoption, and implementation [26] as not all RE-AIM objectives can be met within a feasibility study (i.e. maintenance). This framework [26] has been used to inform the planning of research questions, data collection, and outcomes appropriate for a cRCT feasibility study. This approach to designing our feasibility trial will ensure optimum opportunity to address any issues which arise during implementation and evaluation [26].

Aligned with the applied approach of implementation science, our work [29] is directly influencing clinical guidelines through citations such as the European Society for Clinical Nutrition and Metabolism (ESPEN) Guideline on clinical nutrition in hospitalised patients with acute or chronic kidney disease [30]. Our hope is that through this feasibility trial and subsequent definitive trial impact will continue and research findings will be applied into multimodal interventions [31] to help individuals experiencing or at risk of kidney cachexia maintain body weight, and improve strength to enhance their capacity for independent functioning [1]. Using implementation science, we have developed an in-depth understanding of what is needed, how, and why MMIEAD should achieve impact and have designed the components and processes on best evidence available to achieve the strongest external validity possible [32, 33]. The aim of this paper is to describe the study protocol for the cRCT of the MMIEAD intervention.

## Methods/design

### Aim and objectives

#### Primary aim

To determine the feasibility and acceptability of the MMIEAD intervention for adult patients with renal cachexia.

#### Objectives

i.To determine patient recruitment, retention, and adherence rates (to all 3 components of MMIEAD).ii.To ascertain key considerations for a definitive UK-wide trial including suitability of outcome measures and their potential impacts and data collection burden; optimal study design (including randomisation procedure); and multicomponent intervention design.iii.To conduct a qualitative process evaluation to assess intervention acceptability and practicality with HCPs and patients.iv.To assess the feasibility of conducting a definitive economic evaluation of MMIEAD for patients receiving haemodialysis by testing data collection techniques and suitability of outcome measures.

### Study design and frameworks

The MMIEAD study will deliver a 12-week multimodal intervention using a feasibility cRCT design with a process and economic evaluation. Intervention arm (MMIEAD and standard care) vs. control (standard care). This study will use the conceptual framework PRISM [26] and RE-AIM [27] to enable systematic consideration of the strengths and weaknesses of MMIEAD.

PRISM will address context by considering aspects relevant to this feasibility trial:perspectives on the intervention;the external environment;the implementation and infrastructure; andthe characteristics of those involved in delivering and receiving an influence programme adoption and implementation

Four of the five dimensions included in the RE-AIM framework apply to the parameters of the proposed study:Reach - describes the number, proportion and representativeness of the patients and HCPs who participate in the research study;Effectiveness – the impact of the intervention on outcomes (given the nature of this trial, we will focus on the feasibility of outcome measures);Adoption – the willingness of participants who initiate the intervention to complete it; andImplementation – fidelity of intervention protocol and consistency of implementation across recruitment sites.

The fifth dimension “maintenance” refers to on-going implementation into routine care for at least 2 years post-intervention and is therefore beyond the scope of this feasibility study.

### Phases of the study

The MMIEAD study has been categorised in three phases as follows:

In phase 1, we will deliver MMIEAD, a 12-week multimodal intervention using a feasibility cRCT design to the intervention sites, and collect outcome measures at three timepoints from both intervention and control sites. In phase 2, we will conduct a process evaluation to assess intervention acceptability and practicality with HCPs and patients, and in phase 3, the feasibility of conducting a definitive economic evaluation of MMIEAD will be assessed.

#### Randomisation

Cluster sites have been randomly placed in either the multimodal and standard care group (intervention group) or the standard care group (control group). Two sites have been randomised to intervention, and two have been allocated to control centrally using a computer-generated randomisation schedule (Nquery) independently by a statistician from Northern Ireland Clinical Trials Unit (NICTU). For pragmatic reasons, the personnel who will approach participants regarding the trial will have access to the random allocation sequence and participants will be made aware of their allocation.

#### Blinding

Due to the nature of the intervention, neither patients nor HCPs can be blinded.

####  Study setting

The research will be conducted in four outpatient haemodialysis sites within the UK. This multi-site approach enhances the diversity of patient demographics and service delivery models represented, strengthening the generalisability and relevance of the feasibility findings.

### Characteristics of participants

For inclusion *criteria and exclusion criteria* for patients, please see Table 1 below.

**Table 1 Tab1:** Inclusion and exclusion criteria for patients

**Renal population**	
**Inclusion criteria**	**Exclusion criteria**
CKD stage 5 patients receiving maintenance HD therapy for >3 months, have unintentional weight loss of at least 5% in 12 months or BMI less than 20 kg/m^2^, who have self-reported decreased physical function/muscle strength and appetite, increased fatigue, who are male or female, aged >18 years, and able to provide written informed consent.	Patients under 18 years of age
	Patients within 3 months of initiation of HD (patients in this time frame are generally less clinically stable, many having vascular access procedures performed and with much higher rates of intercurrent events, including death and hospitalisation).
	Patients experiencing weight loss due to clinically explainable reasons for example malabsorption or oesophageal blockage.
	Patients already receiving chronic anticoagulation therapy or with a history of bleeding with 3 months/active bleeding issues.
	Patients receiving immunosuppressants or immunomodulators.
	Patients who are pregnant or breast feeding.
	Patients with a hypersensitivity to any of the constituent components of the omega-3 dietary supplement
	Patients who have dementia, a psychiatric disorder (who are not treated and stable) or a severe cognitive impairment which would deem them unable to give informed consent.
	Patients with expected survival on dialysis of <6 months (e.g. those with severe heart failure (New York Heart Association ≥3)).
	Patients for whom dialysis withdrawal is being considered.
	Patients likely to receive a live-donor transplant or transfer to peritoneal dialysis during the study duration.
	Patients with bilateral lower limb amputations.
	Patients unable to walk without aids or assistance.
	Patients deemed to be clinically unstable by their treating physician.
	Patients who are non-English speaking (not having the ability to provide informed consent, read, and write English).
	Patients who are currently enrolled in any study which involves exercise, fish oil/omega-3, or have been taking fish oil or omega-3 supplementation in the previous 3 months.
	Are not able/willing to be involved.

For inclusion and exclusion criteria for HCPs, see Table 2 below.

**Table 2 Tab2:** Inclusion and exclusion criteria for HCPs

**Healthcare professionals**	
**Inclusion criteria**	**Exclusion criteria**
18 years of age and over	Informal carers
Currently working within the intervention or control sites as a healthcare professional for three months or over.	
Caring for a patient enrolled in the study with end-stage kidney disease and in receipt of haemodialysis.	No involvement in or exposure to the study.
Can provide informed consent, read and write in English.	
Able/willing to be involved.	

### Description of the intervention

#### The components of MMIEAD are as follows

##### Intervention arm (MMIEAD and standard care)

In addition to their standard haemodialysis care, the intervention group will receive MMIEAD, an individualised exercise programme, oral omega-3 supplementation, and dietary advice. All study sites have been surveyed to ensure the intervention components are not provided in standard care, e.g. combined specialist dietetic support with individualised exercise programmes in haemodialysis management.

##### Individualised exercise programme

Mechanical tension induced by aerobic and resistance exercise can increase the rate of metabolic stress and stimulate subcellular pathways involved in muscle protein synthesis which may play a role in exercise-induced muscle growth [34]. Aligned with PRISM [26], exercise components have been co-designed by patients, physiotherapists, and expertise within the research team and are based on the EXACT exercise intervention for patients with advanced cancer [35]. Each participant will receive an exercise handbook and exercise diary to complete daily consisting of 12-week home-based progressive, moderate-intensity walking, and resistance exercise, two–five times per week. Participants will have the flexibility to complete walking and resistance exercises consecutively or separately based on readiness (e.g. symptom burden) or preference, and modifications will be made. Moderate-intensity walking has been defined in the handbook and will be explained to participants using simple, standardised guidance based on the Borg Rating of Perceived Exertion (RPE) scale and functional descriptors. Specifically, participants will be advised that moderate intensity corresponds to an RPE of 12–13 (“somewhat hard”) and should feel like a pace at which they are breathing faster but can still maintain a conversation. This autoregulated programme will involve muscle strengthening and balance retraining exercises, progressing in difficulty over the 12 weeks. Autoregulation refers to the permission of dose modifications to reduce the intensity of exercise and catch up on missed exercise based on individual readiness and has been pivotal in delivering exercise for patients where the disease burden is complex [35]. The exercise programme was informed by the EXACT trial [35], including the use of body mass exercises, dumbbells, and household items to ensure accessibility. During the co-design process with patients, carers, and multidisciplinary stakeholders, modifications were introduced to enhance acceptability and feasibility for adults receiving haemodialysis with cachexia. These refinements included tailoring exercise options to accommodate the functional capacity of those receiving HD. The final programme comprises a structured core set of exercises adapted from EXACT, with individualisation based on the physiotherapist/suitably qualified member of the research team’s initial assessment and weekly reviews. The intervention incorporates established behaviour change techniques (BCTs) to support engagement with the exercise intervention, including goal setting, action planning, self-monitoring, problem-solving, and feedback on behaviour. These techniques are embedded within patient-facing booklets to promote adherence to the exercise sessions programme. Patients will be reviewed by the physiotherapist at the start of the intervention and at 6 weeks to assess their ability to engage in the exercise component and competency to progress.

##### Dietary advice

Dietary advice focuses on adequate dietary protein intake to promote systemic protein anabolic effects required to treat severe muscle wasting [36]. Each patient in the intervention group will receive a 60-min personalised dietetic assessment. Specific to this study, this dietetic programme will focus on adequate dietary protein and energy intake to promote systemic protein anabolic effects required to treat severe muscle wasting (e.g. Kidney Disease Outcomes Quality Initiative (KDOQI) Clinical Practice Guideline For Nutrition in Chronic Kidney Disease: 2020 Update: dietary protein intake of 1.0–1.2g/kg 35 kcal/kg per day adjusted to ideal body weight and standardised across intervention sites) [37]. In addition, this programme will take account of patients’ co-morbidities in relation to dietary advice provided. Patients will be reviewed by the dietician at the start of the intervention and at 6 weeks. Patients will also complete a 3-day food diary on 5 occasions throughout the 12 weeks of the interventions (weeks 1, 3, 6, 9, 12).

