### Analyses

#### Quantitative analysis (phase 1)

Quantitative data will be coded and entered into the Statistical Package for the Social Sciences (IBM SPSS Statistics Version 24). Data on participant eligibility, recruitment, refusal, and retention will be assessed as proportions and rates. Demographic characteristics and adherence to the intervention components will be reported with descriptive statistics as appropriate, for instance, reporting of mean standard deviation (SD) for interval scale variables and frequency/percentages for categorical variables. Differences between control and intervention groups at baseline will be assessed using chi-squared tests and independent *t*-tests. Potential effective outcomes will estimate the effect size and be analysed for mean change using pair sample *t*-tests to compare the difference pre and post intervention, and repeated measure analysis of variance (ANOVA) to consider interactions. However, given that this is a feasibility study, no inferences will be made regarding statistical significance, given that the sample size is not powered to make such assertions. Data from the 3-day food diary will be entered into Nutritics for diet analysis to estimate dietary protein and energy intake. By using Nutritics software (www.nutritics.com - version 3.1), this will enable analysis of compliance with food-based dietary guidelines [63].

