**Effectiveness**			
Overall feasibility	Adherence data – exercise diaries, 3-day food diaries, tablet count (intervention sites only) Weekly log (from phone calls) Outcome measures Record of AEs and SAEs Patient interviews	% of patients who completed exercise diaries and 3-day food diaries. Nutritics for diet analysis, assess adherence to dietetic advice % of patients who consumed recommended intake of omega-3 fatty fish oil. Identify reasons why adherence potentially affected % outcome measures completed % of related AEs/SAEs Burden of outcome measures	Intervention characteristics: Was MMIEAD adaptable to each individual patient and does it indicate that it is beneficial without causing any harm? (intervention only) Recipient experience: Did patients’ perceptions indicate that the MMIEAD intervention could improve QoL? (intervention only)
Variations in feasibility	HCP interviews	Identify barriers, facilitators, potential reasons for variations in feasibility.	
Patients’ satisfaction with the intervention (intervention sites only)	Patient interviews	Questions on acceptability of trial organisation, physical activity dietary advice, nutritional supplement weekly support.	

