Progression to a definitive RCT will be determined by recruitment rates and the acceptability of the intervention for patients and staff. When developing progression criteria, the use of guidelines is suggested, rather than using strict thresholds, to allow for appropriate interpretation and exploration of potential solutions [75]. For example, Pearson and colleagues [69] recommend the use of a traffic light system with varying levels of acceptability. Therefore, compliance with the multimodal intervention will be assessed according to individual components (e.g. number of exercise sessions/tablet count) and thresholds of <50%, 50–80%, and >80%. Compliance of ≥50% of the specific intervention in ≥50% of patients will be considered acceptable; the appropriateness of which is outlined in previous multimodal interventions in cachexia management [78]. Progression to a full trial will be contingent on the acceptability of the intervention for both patients and staff regardless of recruitment rates which will be assessed within the qualitative process evaluation [66]. Any necessary modifications identified within the process evaluation to improve the intervention will be made prior to progression to a definitive trial [76].

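### No food diary is secured before the first dietetic contact and dietary compliance has no stated unit, so unchanged eating could count as adherence

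*Protocol article*

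**What the plan says.** The first objective asks for adherence rates for each of the three intervention components, so diet has to be judged separately.

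**Advice.** Under Dietary advice: "Each patient in the intervention group will receive a 60-min personalised dietetic assessment" and "Patients will be reviewed by the dietician at the start of the intervention and at 6 weeks". The intake reference, introduced as an example from a guideline, is "dietary protein intake of 1.0–1.2g/kg 35 kcal/kg per day adjusted to ideal body weight and standardised across intervention sites".

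**Diaries.** The same section schedules them: "Patients will also complete a 3-day food diary on 5 occasions throughout the 12 weeks of the interventions (weeks 1, 3, 6, 9, 12". Table 3 (Effectiveness) lists them as adherence data from intervention sites only. The outcomes section, from Primary outcome to Mortality, includes appetite but no measure of dietary intake at baseline, 6 or 12 weeks in either arm.

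**Use of the diaries.** Quantitative analysis (phase 1) says: "Data from the 3-day food diary will be entered into Nutritics for diet analysis to estimate dietary protein and energy intake", and that "this will enable analysis of compliance with food-based dietary guidelines". Table 3 gives both the percentage completing diaries and "Nutritics for diet analysis, assess adherence to dietetic advice".

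**Progression.** The Discussion sets bands of below 50%, 50–80% and above 80% for each component, naming exercise sessions and tablet count as examples. It then states: "Compliance of ≥50% of the specific intervention in ≥50% of patients will be considered acceptable". No dietary unit is named.

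**The concern.** Dietary advice is meant to alter what people eat. With no diary secured before it and none in the control arm, an intake at or near target looks the same whether the patient followed the advice or always ate that way.

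The progression rule makes this matter more. Sessions and tablets start from zero, so 50% of them means something was taken up. Food intake never starts from zero, so a percentage of an intake figure can be high with no uptake at all. The dietary adherence rate is one of three component rates feeding the decision on a definitive trial, and a pass could be read as evidence that the advice was followed.

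**Working it through.** The plan states no computed figure on this point, so there is nothing to reproduce. The check has two parts.

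**1. Timing**

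| Event | When | Who |
|---|---|---|
| Baseline outcome measures | Before the intervention starts | Both arms; no diet measure listed |
| Dietician contact | Start of intervention, week 6 | Intervention arm |
| Food diaries | Weeks 1, 3, 6, 9, 12 of the intervention | Intervention sites |

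Diaries scheduled before the intervention: 0 of 5. Control-arm diaries: 0. The natural reading puts the week 1 diary after the first dietetic contact, but the order within week 1 is not stated.

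**2. What 50% could mean for diet**

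*Reading A: half the intake reference.*
- Protein: 0.5 × 1.0 = 0.5 g/kg and 0.5 × 1.2 = 0.6 g/kg per day.
- Energy: 0.5 × 35 = 17.5 kcal/kg per day.
- At an assumed ideal weight of 60 kg: 30–36 g protein against 60–72 g, and 1050 kcal against 2100 kcal.
- A patient eating an assumed 0.8 g/kg before and after the advice scores 0.8/1.2 = 67% to 0.8/1.0 = 80%, and passes with no change.

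The arm-level consequence can be illustrated. Assume unchanged usual intake is normal with mean m and SD s, and let c be the cut-off. The share classed adherent is p = 1 − Φ((c − m)/s). With 20 intervention patients, half means at least 10, and the chance of passing is P(X ≥ 10) for X ~ Binomial(20, p). For example, m = 0.8, s = 0.2, c = 0.6 gives p = 1 − Φ(−1) = 0.84. None of the means and SDs below comes from the document.

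| Assumed unchanged intake | Cut-off | Share classed adherent | P(at least 10 of 20) |
|---|---|---|---|
| Protein mean 0.5 g/kg, SD 0.2–0.3 | 0.5–0.6 | 31–50% | 0.06–0.59 |
| Protein mean 0.6, SD 0.2–0.3 | 0.5–0.6 | 50–69% | 0.59–0.98 |
| Protein mean 0.8, SD 0.2–0.3 | 0.5–0.6 | 75–93% | above 0.99 |
| Energy mean 15 kcal/kg, SD 5–8 | 17.5 | 31–38% | 0.06–0.18 |
| Energy mean 20, SD 5–8 | 17.5 | 62–69% | 0.91–0.98 |

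Protein and energy are scored separately here; a rule requiring both would pass fewer patients. For contrast, a cut-off at the full lower protein figure (1.0 g/kg), with unchanged means of 0.7–0.9 g/kg and the same SDs, classes 7–37% as adherent, and the chance of reaching 10 of 20 runs from under 0.001 to 0.16.

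*Reading B: diary completion.* 3 of 5 diaries is 60%, which passes whatever is eaten.

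*Reading C: share of diaries or days on target.* This is equally open, and under it unchanged eating below target would not pass.

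**The case against.** Much of the other side stands.

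- **The rule is not tied to an intake target.** A reader might infer that the 50% rule is applied to the protein and energy figures. The document does not say so. Those figures are an example within a personalised assessment, and the Discussion names no dietary unit. Reading A is a possibility only.
- **The unit may be defined elsewhere.** How compliance is scored for diet is detail that a full protocol or analysis plan could supply. Its absence from an article would not be a finding by itself.
- **Week 1 order is open.** A reader might conclude that all five diaries certainly follow the advice. A week 1 diary kept before or alongside the assessment is not excluded, but the schedule does not secure it.
- **Diaries are not the only source.** The weekly telephone log covers dietary adherence, and Table 3 adds patient and staff interviews. It would be too strong to say that the trial cannot tell whether advice was followed.
- **Adherence is not change.** A patient already at target who stays there is legitimately adherent to advice on adequate intake, and comparison with a guideline level needs no baseline. The difficulty arises when a low percentage of a level is read as uptake.
- **Progression is not mechanical.** The Discussion prefers guidelines to strict thresholds and makes progression contingent on qualitative acceptability.

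What remains is the missing pre-advice diary. An analysis plan can define a unit later, but it cannot recover a diary that was never kept.

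**Conclusion.** The point holds as a modest, inexpensive improvement. The stated schedule does not secure any measure of intake before the first dietetic contact, and there is none in the control arm, so the diaries give intake level but not change after advice. Separately, 50% compliance is undefined for diet, and two of the open readings would let unchanged eating pass.

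The size is conditional. If the rule meant half the intake reference, the chance of declaring the component acceptable with no dietary change runs from 0.06 to above 0.99 across the assumed usual intakes, and fades when usual intake is near or below half the reference. The document gives no usual intake, and without a pre-advice diary the trial may not learn which case applies. It is not established that the component will be passed wrongly, and nothing here bears on which intake target is right.

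**What to change.** 1. **Move the first diary.** Have it completed at baseline, before the dietetic assessment, so the five diaries fall at baseline and weeks 3, 6, 9 and 12. Because it covers three days, it must be handed out early enough to finish before that contact.
2. **Report change from it**, descriptively. With no control diaries, the change is a before-and-after comparison and should not be attributed to the advice.
3. **Name the dietary unit for the progression rule:** the share of post-advice diaries in which intake meets the individual's own dietitian-set target. At 50%, that is at least 2 of 4 diaries in at least 10 of 20 patients. Do not use diary completion or half the target. State in advance how near-misses, and diaries meeting protein but not energy, are scored; report mean percentage of target alongside so the yes/no score does not hide them.

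**Cost.** Protocol wording and an earlier hand-out, with no extra diary or staff. The week 1 post-advice diary is lost, and reported compliance may be less favourable. Patients already enrolled may lack the pre-advice diary. Recruitment began on 08.09.25, and at the anticipated two patients per month per site, 10 per site takes 10/2 = 5 months, to about 8 February 2026, before the article's publication on 19 February 2026. Actual accrual is not given. If recruitment is largely complete, item 3 can still be done now, and item 1 carries over to the definitive trial.
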